The MiTy trial, which showed an association with SGA in the metformin-treated group, recently published data about the infants of these mothers at 2 years and found their anthropometric measures were similar between groups at the 2-year endpoint, but that metformin-exposed male infants had a different growth trajectory, and that BMI was higher from 6 to 24 months [34]. Postnatal catch-up or accelerated growth often defined as a delta weight SD score > 0.5 or 0.67 has been consistently associated with insulin resistance and metabolic syndrome-related disorders (e.g. type 2 diabetes) in later life [35–37]. Accelerated growth during early postnatal life, irrespective of birth weight, has been shown to associate with changes in β-cell function at 12 months [38, 39] and appears to be particularly important for metabolic health in later life [40]. It is unclear from existing studies whether metformin exposure in utero affects postnatal catch-up and therefore impacts future cardiometabolic health in later life. Of note, infants exposed to metformin in the EMPOWaR study [41], a randomised study of obese pregnant women, were thinner (lower ponderal index) at birth, which, if associated with accelerated postnatal weight gain (akin to the mouse studies), could confer an increased cardiometabolic risk to the offspring [42].

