### Outcomes {12}

#### MIMICH

Outcomes will be recorded in the electronic case report form, hosted on REDCap. Outcomes will be collected from baseline to maternal discharge post-birth. Neonatal outcomes will be recorded up to 28 days after birth.

Primary outcome:

Third trimester foetal growth velocity, assessed by change in foetal growth z-score between 20 and 29 weeks’ gestation (average) and birth.

At each scan, the estimated foetal weight (EFW) in grams will be calculated using 2D biometry and fractional thigh volume (TVol) measurements using a standard formula [44] and converted to a z-score [43]. The delta change in z-score between the average z-score of scans performed between 20 and 29 weeks and the birthweight z-score will be calculated.

Secondary outcomes:

During pregnancy, secondary outcomes will be reported as per standard for pregnancy intervention trials. Secondary foetal growth and birthweight analyses will be assessed according to treatment group in line with the primary outcome analysis. Outcomes relating to blood glucose control (as an indicator of treatment effect) will similarly be compared between groups, as will blood pressure and hypertensive complications. Reporting and analysis of secondary outcomes will be described in full in the statistical analysis plan; to avoid issues of multiple testing, not all secondary outcomes will be compared between treatment groups. Secondary outcomes will be assessed using adjusted linear regression for continuous outcomes and chi-squared for categorical outcomes; *p* values > 0.01 and < 0.05 will be interpreted with caution. Where appropriate, outcomes will be presented with a treatment effect and confidence intervals; other outcomes will be presented with summary statistics only.

Prespecified secondary outcomes:

Adherence/acceptability:Number of missed doses—calculated as an average over pregnancy from the number of missed doses reported in the 7 days prior to each study visit (adjusted for number of study visits)Number of women unable to comply with allocated treatment (cross over)Undesirable effects of allocated treatment (number of women reporting undesirable effects associated with metformin and/or insulin/number of women receiving metformin or insulin treatment)Treatment satisfaction with allocated medication regime (questionnaire)Acceptability of allocated medication regime (questionnaire)

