### Sample size considerations {14}

The primary outcome is a change in foetal growth velocity in the third trimester. Our group has pioneered the use of volumetric ultrasound techniques to improve the detection of foetal growth abnormalities [47, 48]. Previous studies investigating hypoglycaemic agents in pregnancy have used birthweight as the primary outcome, which provides only a crude estimate of foetal growth. In pregnancies where there are conflicting exposures influencing foetal growth and placental function (e.g. hypertension and hyperglycaemia), absolute birthweight is not sufficient to detect subtle, but clinically significant changes in foetal growth and placental function. To address this limitation, in this study, longitudinal measures of foetal growth will be used to quantify the deviation in foetal growth in the third trimester. This will be derived from the delta z-score in estimated foetal weight (using the modified EFW TVol formula [44]) over the third trimester using WHO foetal growth charts [43]. This will provide a more sensitive assessment of the effect of metformin on foetal growth than birthweight alone; the use of a continuous measure as a primary outcome also makes the study more efficient as it requires a smaller sample size. In order to verify the primary outcome, the eCRF will capture the TVol measurement and the EFW at each scan as well as recording the 2nd trimester and 3rd trimester deviation scores. The source data (scan report) will verify the 2D biometry.

In a comparison of women with type 2 diabetes treated with metformin recruited to the VELOCITY study, the mean delta z-score between the second trimester and birth was − 0.51 (SD 1.1) for women with a placental disease risk factor (*n* = 34) and 0.30 (SD 0.9) in women without a risk factor (*n* = 45). A sample size of 190 women (95 in each group) will provide 80% power to detect a clinically significant difference in delta z-scores of 0.41 (SD 1.0) between the treatment groups; this difference would reflect a rightward shift in the birthweight distribution in women in whom metformin was withheld to a mean of − 0.1.

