An adjusted analysis of the effect of the intervention (withholding metformin) on foetal growth will include covariates (mean daily glucose, time in target) which are known to influence foetal growth to improve the precision of the treatment effect as appropriate. Change in foetal weight z-score provides a continuous measure of late pregnancy growth trajectory derived from early foetal biometry and 3D volumetric measurements and therefore the foetus is its own control. Importantly, this removes the need to adjust for infant sex. Furthermore, as the measurement of foetal weight z-scores using 3D foetal thigh volumes, and therefore calculation of delta z-scores is done after birth, the risk of bias is minimised. In the MiTy trial [11], a comparison of metformin vs no metformin in unselected women with type 2 diabetes, the difference in birthweight z-score was − 0.28 (− 0.45 to − 0.10).

Recruitment figures have been based on attendances to the Manchester Antenatal Vascular Service (MAViS) clinic, which provides care for women with cardiometabolic disease, and the diabetes service across Manchester Foundation Trust. Allowing for the fact that the proposed study will draw from a population of 16,500 pregnancies per annum, eligible women will include those with type 2 diabetes (*n* ≈ 108) and women who develop GDM with additional risk factors for placental disease (*n* ≈ 420). A recruitment rate of 50% would yield an available cohort of approximately 225 women (10% dropout) over a 36-month time frame. Based on figures from the MAViS cohort, 20% would be expected to develop a small for gestational age (SGA < 10th centile) and 12–18% pre-eclampsia.

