### MIMICH sequence generation {16a}

The sequence will be computer generated within the Sealed Envelope platform. Participants will be randomised (1:1) using minimisation with a random element controlling for:Type of diabetes (diagnosed < 24 weeks’ gestation, diagnosed > 24 weeks’ gestation)Risk factor for placental disease (uteroplacental or maternal risk factor)Gestational age (6 + 0 to 11 + 6 weeks, 12 + 0 to 23 + 6 weeks, 24 + 0 to 30 + 0 weeks)

The sequence will be computer generated. Participants will be randomised (1:1) using minimisation with a random element controlling for:Type of diabetes (diagnosed < 24 weeks’ gestation, diagnosed > 24 weeks’ gestation)Risk factor for placental disease (uteroplacental or maternal risk factor)Gestational age (6 + 0 to 11 + 6 weeks, 12 + 0 to 23 + 6 weeks, 24 + 0 to 30 + 0 weeks)

For each new participant, the algorithm calculates the imbalance that would result from assigning them to each treatment arm. The arm that minimises imbalance is selected with high probability (default 80%). With the remaining probability (20%), allocation is made to the alternative arm. If both arms would produce equal balance, allocation is determined with equal probability (50:50).

This approach maintains a close balance between groups across important prognostic factors, whilst the random element preserves allocation unpredictability. The randomisation sequence is generated and maintained centrally within the Sealed Envelope system, ensuring full allocation concealment from investigators and participants until the point of assignment.

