## Statistical methods

### Statistical methods for primary and secondary outcomes {20a}

The statistical analysis will be conducted according to the approved statistical analysis plan. Baseline characteristics of the trial population will be presented as mean and standard deviation (or median and interquartile range as appropriate). The main analysis will be an intention to treat analysis for the primary and secondary outcomes. For the primary outcome, the average z-score for estimated foetal weight (calculated using the modified EFW formula which incorporates TVol [44]) performed between 20 and 29 weeks will be calculated. This will be 1–3 scans per woman. The delta between the birthweight z-score and the 20–29-week z-score will be calculated. Delta z-scores will be compared between treatment groups using linear regression models adjusted for baseline z-score and minimisation variables (these will be confirmed in the final statistical analysis plan). All secondary outcomes will be reported as described in the outcomes section and analysed in accordance with the prespecified statistical analysis plan.

Missing data for baseline prognostic factors are not anticipated since they must be recorded to allocate treatment. All observed outcome data will be included in the analyses. As this is an exploratory study, we will focus on reporting the amount of missing data. We will report the number (%) of participants withdrawing fully from the trial and lost to follow-up by treatment arm. Reasons for missingness may be important, and these will be tabulated by treatment arm and documented as far as possible. Main analyses will be performed using STATA (StataCorp, College Station, TX, USA).

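### The stated reason for not adjusting for infant sex does not hold; the effect on precision is small and the primary estimate stays unbiased

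*Protocol article*

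**What the plan says.** The primary outcome is a difference of two z-scores (Outcomes {12}, MIMICH): "The delta change in z-score between the average z-score of scans performed between 20 and 29 weeks and the birthweight z-score will be calculated".

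Sample size considerations {14} describes this change as "derived from early foetal biometry and 3D volumetric measurements and therefore the foetus is its own control". The next sentence draws the consequence: "Importantly, this removes the need to adjust for infant sex".

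Statistical methods for primary and secondary outcomes {20a} sets the primary analysis as "linear regression models adjusted for baseline z-score and minimisation variables", with confirmation left to the final SAP. Sex is not among the three minimisation factors in MIMICH sequence generation {16a}, which are type of diabetes by timing of diagnosis, type of placental risk factor, and gestational age.

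The z-scores come from WHO charts (reference 43). The article does not say whether a sex-specific version is used at either time point, and it gives no estimate of a sex difference in delta z.

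**The concern.** The sentence makes a statistical claim: differencing within a foetus takes care of sex. That is true only for a sex offset that is the same, in z units, at both ends. The outcome is growth between the two ends, so a sex difference in that growth passes into the delta in full. The two ends are also measured differently. One is an average of ultrasound weight estimates from one to three scans, and the other is a birthweight, so equal offsets cannot be taken for granted.

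Infant sex is fixed before randomisation, cannot be changed by treatment and is not balanced by the minimisation. That makes it a legitimate baseline covariate. The same section accepts adjustment for other covariates in order to improve precision, yet it argues against this one on grounds that do not hold. At stake are some precision and some protection against chance imbalance in a trial of about 95 per arm.

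**Working it through.** **Inputs from the protocol article.** Sample size considerations {14}: 95 per group, difference 0.41, SD 1.0, power 80%. Model: {20a}.

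**Assumptions.** Two-sided alpha of 0.05 (not stated for the sample size); equal numbers of boys and girls; a male-female difference g in delta z of 0 to 0.4.

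**1. The plan's own figure.** The normal approximation gives 2 × (1.96 + 0.8416)² / 0.41² = 93.4, so 94 per arm. The noncentral t calculation gives 95 per arm with 80.3% power. The stated 190 is reproduced, and nothing below changes it.

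**2. What differencing removes.** Let the male-female offset be s₁ at 20–29 weeks and s₂ at birth. The offset in delta z is s₂ − s₁, which is zero only if s₁ = s₂.

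**3. What the planned model does.** Regressing (birth z − baseline z) on treatment and baseline z gives the same treatment coefficient as regressing birth z on treatment and baseline z. If the slope of birth z on baseline z within each sex is b, a constant offset s at both times leaves s − b × s = s(1 − b). For illustration, s = 0.3 and b = 0.5 leave 0.15. Full cancellation needs b = 1. So the baseline adjustment partly undoes the cancellation on which the sentence relies.

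**4. Precision gained by adding sex.** With a 50:50 split, sex explains R² = g²/4 of the variance (SD 1.0). The residual SD is √(1 − g²/4) and the treatment SE is that residual SD × √(2/95). Power is from the noncentral t with one further degree of freedom spent. Baseline adjustment is left out here, to stay on the scale of the plan's own calculation.

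| g (assumed) | R² | SE of treatment effect | Power |
|---|---|---|---|
| 0 | 0 | 0.1451 | 80.3% |
| 0.1 | 0.25% | 0.1449 | 80.4% |
| 0.2 | 1% | 0.1444 | 80.7% |
| 0.3 | 2.25% | 0.1435 | 81.2% |
| 0.4 | 4% | 0.1422 | 81.8% |

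**5. Chance imbalance.** The SD of the difference in proportion male between arms is √(2 × 0.25 / 95) = 0.0725, so 2 SD is 0.145. The shift in the estimate is g × 0.145:

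- g = 0.1: 0.0145, or 4% of 0.41
- g = 0.2: 0.029, or 7%
- g = 0.3: 0.0435, or 11%
- g = 0.4: 0.058, or 14%

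The largest of these is 0.058 / 0.1451 = 0.40 of a standard error.

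**6. Cost if sex does not matter.** The baseline-adjusted model was simulated with 95 per arm, b = 0.5, delta SD of 1 before any sex effect is added, and 4,000 runs per setting. The mean treatment SE, without and then with sex, was:

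- no sex effect: 0.1257 and 0.1260
- constant offset of 0.3 at both times: 0.1263 and 0.1262
- offset of 0.1 at baseline and 0.3 at birth: 0.1274 and 0.1264

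The residue from a constant offset (step 3) is real but makes almost no practical difference. A sex difference in growth matters a little more.

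**The case against.** The strongest reply is that the word need is defensible. Under randomisation the estimate is unbiased without sex in the model. Chance imbalance in sex is already part of the residual variance, and so of the confidence interval. This stands. A reader might infer that the primary comparison is biased or its interval invalid, and neither is so.

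Second, the sentence is a rationale in the sample size section and not an analysis rule, and the SAP is to confirm the adjustment variables. So the plan does not forbid sex as a covariate. That also stands, but leaving the list to the SAP does not repair an affirmative argument, in the published text, against using it.

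Third, if reference 43 supplies sex-specific z-scores and they are used at both time points, most of the sex effect is already gone. The article's silence does not show otherwise. In that case, though, the charts would be the reason to leave sex out. The own-control argument would still be wrong.

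Fourth, it is tempting to cite the background statement that "metformin-exposed male infants had a different growth trajectory" as proof of a sex effect. It is not: it describes growth after birth and a difference by treatment within one sex. It does not show a sex difference in delta z from 20–29 weeks to birth.

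Finally, one might extend the point to MIMICH II or ask for an arm-by-sex interaction as a correction. The documents support neither. The MIMICH II sample size text does not use this argument or exclude sex, and an interaction would be an additional analysis, not the repair of an error.

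**Conclusion.** The point holds as a minor one. The argument given for leaving out infant sex is incorrect whether or not the charts are sex-specific. The consequence is limited to precision and chance imbalance: at most about 1.5 power points (80.3% to 81.8%), and a shift of at most about 0.06 at a 2-SD imbalance. Both maxima sit at the top of an assumed range of 0 to 0.4 for the sex difference in delta z, and the shift also needs an unusual imbalance. The gain is nil if sex has no effect on delta z, and near nil if the z-scores are already sex-specific. Calling it a free gain would therefore overstate it. The sample size is unaffected.

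**What to change.** 1. In Sample size considerations {14}, delete the sentence on infant sex, or reword it to say that the change score removes only a sex offset common to both time points.
2. State whether the z-scores from reference 43 are sex-specific, for the 20–29-week estimates and for birthweight alike.
3. In {20a} and the SAP, prespecify infant sex as a covariate in the primary model, alongside the baseline z-score and the minimisation variables.

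The cost is a line of text and one degree of freedom. If sex has no effect, the loss of precision is negligible (simulated SE 0.1260 against 0.1257). Sample size and trial conduct do not change.

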**Methods:**

MIMICH is a randomised control trial (RCT) comparing routine treatment for diabetes, the standard of care, to withholding metformin (the intervention) during pregnancy, in women with type 2 diabetes or gestational diabetes (GDM) who have maternal or uteroplacental risk factors for placental disease in a target sample of 225 participants. Participants receive the recommended schedule of antenatal care, including serial biometry ultrasound with the addition of fractional thigh volume measurement. The primary outcome will be change in estimated weight z-score from second trimester to birth. The MIMICH II study will follow up the mothers and infants at 3–6 months and 12–15 months after pregnancy. Study procedures include anthropometric measurements from both mother and baby, data collection about medications, complications after birth and feeding, and maternal blood sampling. Infant echocardiography, blood pressure measurements and venepuncture will also be undertaken where possible.

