### Trial design {8}

MIMICH is a phase III, two-arm, single-centre, open-label pragmatic randomised controlled trial (RCT). The study framework aims to assess the superiority of withholding metformin in otherwise standard pregnancy diabetes care, determined by foetal growth trajectory and placental function. Randomisation will take place in a 1:1 ratio. Following the RCT, participants who provide consent will be enrolled in an observational cohort study assessing postnatal maternal and infant cardiometabolic health, with follow-up visits at 3–6 months and again at 12–48 months postpartum.

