The primary outcome for the postnatal follow-up study will be weight gain trajectory, determined as change in weight z-score, between birth and 12 months of age. Assuming a population z-score weight gain of 0.08–0.12 (SD 0.9) [37, 38] at 3–6 and 12 months, *n* = 39 (*β* = 0.8) or *n* = 70 (*β* = 0.9) per group will be required to show a 0.5 difference in z-score between groups (retention 35–63%). Excessive infant weight gain (> 0.67 SD, representative of the width of each percentile band on standard growth charts (e.g. 2nd–9th, 9th–25th percentile [8]) in the first year of life is strongly associated with an adverse adult cardiometabolic risk profile [36, 37]. Previous studies have demonstrated significant differences in adult cardiometabolic indices between groups of infants with rapid vs slow weight gain in the first 3–6 months after birth [49] using data from 65 and 22 adults, respectively. A conservative 0.5 change in z-score between metformin-exposed and non-exposed infants (at each time point) will therefore represent a robust and important clinical difference. Covariates (maternal glycaemic control, infant feeding, birthweight z-score and infant height) likely to be associated with the primary outcome will be included in the adjusted analysis to improve the precision of the treatment effect as appropriate. This will be balanced against the loss of effective sample size through use of degrees of freedom following inclusion of covariates [50].

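### MIMICH II: 39 infants per group gives about 68% power for a 0.5 z-score difference with SD 0.9, not 80%; 80% needs 52 per group

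*Protocol article*

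**What the plan says.** The section Sample size considerations {14} gives one power statement for the postnatal study, whose primary infant outcome is the change in weight z-score from birth.

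- **Variability:** "Assuming a population z-score weight gain of 0.08–0.12 (SD 0.9) [37, 38] at 3–6 and 12 months". One SD serves both time points.
- **Size and power:** "n* = 39 (*β* = 0.8) or *n* = 70 (*β* = 0.9) per group will be required". The values 0.8 and 0.9 are labelled β but can only be meant as power.
- **Target difference and retention:** "per group will be required to show a 0.5 difference in z-score between groups (retention 35–63" per cent).

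No significance level or sidedness is given for MIMICH II. Covariate adjustment is mentioned as a way to gain precision, but no variance reduction is quantified. For the main trial, the same section states: "A sample size of 190 women (95 in each group) will provide 80% power" to detect a difference of 0.41 with SD 1.0. The abstract's Methods describe the trial as carried out "in a target sample of 225 participants", and Trial design {8} says "Randomisation will take place in a 1:1 ratio".

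**The concern.** For a comparison of two means with fixed difference, SD and alpha, moving from 80% to 90% power raises the sample size by about a third. Here it rises from 39 to 70, which is a factor of 1.79. At least one figure must be wrong.

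MIMICH II recruits only from MIMICH participants, so its power depends on how many mother–infant pairs return. The smaller figure is also the source of the lower retention bound. If 39 is too low, the article presents a follow-up of roughly one third of the cohort as adequately powered when it is not. A null result on infant weight gain at that level of follow-up could then be read as more reassuring about in utero metformin exposure than the data allow.

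**Working it through.** **Inputs**

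- Difference 0.5 z, SD 0.9, 39 or 70 per group, retention 35–63%: Sample size considerations {14}.
- Equal groups: Trial design {8}.
- Target of 225 participants, about 112 per arm: abstract, Methods.
- Two-sided 5%: assumed, and tested in step 3.

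**1. Required size per group.** The normal approximation is n = 2 × [SD × (z for alpha + z for power) / difference]². The first factor is 2 × (0.9/0.5)² = 6.48.

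- 90% power: 6.48 × (1.960 + 1.282)² = 68.1, so 69. The t-test gives 69.1, so 70. **The article's 70 reproduces.**
- 80% power: 6.48 × (1.960 + 0.842)² = 50.9, so 51. The t-test gives 51.8, so 52. **The article's 39 does not reproduce.**

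**2. What 39 per group delivers.** Power is approximately Φ[(0.5/0.9) × √(39/2) − 1.960] = Φ(0.493) = 68.9%. The t-test gives 67.8%. The difference detectable with 80% power is 0.9 × √(2/39) × 2.802 = 0.57 z by the normal approximation and 0.58 z by the t-test. With 52 per group, t-test power is 80.1%.

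**3. Could another alpha explain both figures?** Sizes per group, by t-test:

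| Test | MIMICH II, 80% | MIMICH II, 90% | MIMICH, 80% (0.41, SD 1.0) |
|---|---|---|---|
| Article | 39 | 70 | 95 |
| Two-sided 5% | 52 | 70 | 95 |
| One-sided 5% | 41 | 57 | 75 |

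One-sided 5% comes close to 39 (78.4% power there) but misses the other two figures. Two-sided 5% matches both of those and misses only 39.

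The ratio of the two sizes does not depend on the SD or the difference. It is [(z for alpha + 1.282)/(z for alpha + 0.842)]², which is 1.34 at two-sided 5% and 1.39 at one-sided 5%. The article's ratio is 70/39 = 1.79, whose square root is 1.340. Solving (z + 1.282) = 1.340 × (z + 0.842) gives z ≈ 0.45, a one-sided alpha of about 0.33. The size for 80% power would then be about 6.48 × (0.45 + 0.842)² ≈ 11. No common alpha yields both 39 and 70.

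**4. Could another input explain 39?** At two-sided 5%, 39 per group has 80% power only if the SD is about 0.78 (t-test; 0.79 by the normal approximation), or if covariates explain 1 − 39/50.9 = 23% of the variance (about 25% by the t-test). Neither is stated. Either one would also lower the 90% figure to about 68.1 × 39/50.9 = 52, so the 70 would then be wrong.

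**5. Retention.** 39/112 = 34.8% and 70/112 = 62.5%, which are the printed 35% and 63%. So 39 and 70 are numbers of evaluable infants with no dropout allowance inside them. For 52 per group, 52/112 = 46.4%; equivalently, 104/225 = 46.2%.

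**The case against.** The arithmetic is not in serious dispute; its weight is. MIMICH II is an observational follow-up whose size is set by the parent trial. Its recruitment continues until all MIMICH pregnancies are complete, so nothing stops it at 39 per group. The article presents 35–63% as a range and does not name 35% as a target or success criterion. A confidence interval in the final report would show the precision actually achieved. All of this stands. It limits the damage to a lower retention scenario that is too optimistic, and no treatment or recruitment decision turns on it.

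The planned analysis is also adjusted, with birthweight z-score among the covariates. Because birthweight z-score is part of the change score, some gain in precision is plausible. With 39 per group, an R² of 0.20, 0.25 or 0.30 gives power of 77%, 80% or 83%. So 67.8% is the power of an unadjusted comparison, and the adjusted analysis may do better. But the article states no R², does not say that 39 relies on one, and itself notes that covariates use up degrees of freedom. A gain applied to 39 would have to be applied to 70 as well.

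Finally, alpha is unstated, and under a one-sided 5% test 39 is nearly right. That reading fails because the same sentence's 70 would then have to be 57.

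**Conclusion.** The 80% figure is wrong as written. From the article's own difference and SD, 80% power needs 52 per group (104 infants, about 46% of 225), not 39 (78 infants, about 35%). That is a shortfall of 13 per group. At 39 per group, power is about 68%, so nearly one in three true differences of 0.5 z would be missed rather than one in five. The figure of 70 per group for 90% power is sound.

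The values 52 and 68% rest on an unadjusted two-sample t-test at two-sided 5%, which the article does not state for MIMICH II but which its other two sample sizes imply. The inconsistency between 39 and 70 does not depend on that assumption. This is the only power statement for the MIMICH II primary outcome, so it should be corrected. Writing β for power is a minor slip in the same sentence.

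**What to change.** In Sample size considerations {14}, state that 52 infants per group give 80% power and 70 per group give 90% power to detect a 0.5 z-score difference with SD 0.9 at two-sided 5%. Change the retention range to 46–63%, keeping the article's base of about 112 per arm (on the base of 225 the upper end is 140/225 = 62.2%). Replace β with power.

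If 39 per group is to remain as a practical floor, say that it gives about 68% power, or 80% power for a difference of 0.58 z. If an unstated SD or covariate R² lay behind 39, state it and recompute both figures from it.

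The cost is a text correction. Recruitment to MIMICH does not change, but the minimum follow-up for an 80%-powered comparison rises from 78 to 104 infants.
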